#### Statistical analysis plan

Using data captured during implementation of the *Screen-Triage-Treat* approach for cervical cancer screening, we will evaluate intervention fidelity as a function of 1) *Completion Rate*: the proportion of enrolled women who turned in a self-collected sample for HPV DNA testing; 2) *Test Result Notification Rate*: the proportion of women who were notified of their HPV DNA test result on the same day as sample collection; and 3) *Treatment Rate*: the proportion of screen-positive women who were treated with thermal ablation, if appropriate, or referral for higher level of care.

Patients’ characteristics and clinical values will be summarized in tables and figures. Continuous variables will be presented as medians and interquartile ranges. Categorical variables as frequencies and percentages. Descriptive statistics will be done for the overall population and stratified intervention status and study site. Continuous variables will be compared via the Mann–Whitney-Wilcoxon test, and categorical variables will be compared via the chi-square test. We will use a generalized linear model (GLM) with the logit link to and perform an interrupted time series to assess the impact of the intervention and the proportion of patients who subsequently underwent treatment for cervical cancer. The model will regress the outcome on intervention status (binary variables, yes/no), calendar time (in months), and an interaction between the two terms. By doing this we will be able to assess the immediate impact of the intervention (also known as level change) as well as its effect over time (sustained effect of the intervention) compared to the counterfactual scenario of no intervention being implemented. Analysis and comparisons will be performed overall, combining all sites, as well as being stratified by health facilities. We will adjust for relevant demographic and clinical characteristics, such as age, CD4 count, and viral load, among other factors. Continuous variables will be modeled via restricted cubic splines. We will again use GLM with a gaussian link to estimate the impact of the intervention on the number of WLWH diagnosed with HPV, adjusting for the same covariates as above, and following the same steps as above (e.g., another interrupted time series). If the normality assumption is violated, we plan to use ordinal regression models as an alternative. We do not expect issues with statistical over-fitting.

### Specific objective 3

To use the Consolidated Framework for Implementation Research (CFIR) to identify factors that explain site-level and provider-level variation in the implementation of the *Screen-Triage-Treat* approach to cervical cancer screening utilizing self-collected HPV DNA testing.

Hypothesis: Quantitative and qualitative interviewing with health facility providers will generate important information about intervention uptake and fidelity that will inform subsequent implementation scale-up.

The introduction of a new intervention into a clinical setting is a complex process and requires support and buy-in at each facility. As a hybrid type III effectiveness—implementation study, this proposal is predominantly focused on testing the implementation strategy of our intervention. However, we will also observe and gather information on the clinical intervention's impact on relevant outcomes.

We will conduct a mixed-methods evaluation, employing qualitative, semi-structured interviews and a quantitative survey questionnaire to explore provider experiences with implementing the *Screen-Triage-Treat* approach for cervical cancer screening. We will evaluate constructs from the Consolidated Framework for Implementation Research (CFIR), including perceptions about the *Intervention Characteristics* (e.g., relative advantage of the approach); *Outer Setting factors* influencing use (e.g., perception of patient needs and resources); *Inner Setting factors* impacting uptake and fidelity to the intervention (e.g., compatibility, relative priority, available resources); *Characteristics of Individuals* (e.g., knowledge and beliefs about the intervention); and *Process Factors* (e.g., champions, planning activities) within each health facility. We will look at how these factors influenced uptake and fidelity throughout implementation (Fig. 5).

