### Aims/objectives

The overall aim of this study is to evaluate implementation best practices for deploying a *Screen-Triage-Treat* approach to cervical cancer screening utilizing self-collected HPV DNA testing among HIV-infected women in care within select health facilities in Chókwè District, Mozambique. The main objectives of this study are:To develop an in-depth understanding of the HPV *Screen-Triage-Treat* care cascade within the HIV care and treatment services based on a collaborative, exploration-focused process with local stakeholders.To evaluate the effectiveness of the *Screen-Triage-Treat* approach to cervical cancer screening utilizing self-collected HPV DNA testing.To use the Consolidated Framework for Implementation Research (CFIR) to identify factors that explain site-level and provider-level variation in the implementation of the *Screen-Triage-Treat* approach to cervical cancer screening utilizing self-collected HPV DNA testing.

Table 1 shows the SPIRIT diagram including the schedule of enrollment, intervention, and assessment.

**Table 1 Tab1:** SPIRIT diagram: schedule of enrollment, intervention, and assessment

Study Period	Pre-Implementation Phase	Implementation Phase	Follow-up Phase	Post-implementation Evaluation
Timepoint	Month −2 to 0	Month 0–30	Month 1–30	Month 31–33
Enrollment:				
Site preparation and staff training	X			
Two-week pilot assessment period	X			
Model participant enrollment (1–2/day)		X		
Participant eligibility screening		X		
Informed Consent		X		
Intervention:				
Self-collected HPV DNA testing (Screen)		X		
HPV result reporting (same-day CHC; weekly in periphery)		X		
VIA and thermal ablation if eligible (Triage-and-treat)		X		
Referral to higher level of care for LEEP/colposcopy in not eligible for ablation		X		
Assessments:				
Baseline retrospective data (past 12 months)	X			
Process mapping/group model building workshop and qualitative interviews (Objective 1a-c)	X	X		
Quantitative data collection (HPV, VIA, treatment rates)		X		
Implementation Outcomes (adoption, fidelity, reach, acceptability)		X	X	
Qualitative provider interviews (CFIR domain)			X	
Statistical analysis of primary outcome (proportion of HPV + women treated, Objective 2)			X	
Analysis of secondary outcomes (implementation outcomes, Objective 3)			X	
Dissemination workshops and final reporting				X

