#### Laboratory procedures at CHC

Directly following collection of the vaginal swab sample, the participant will be taken back to the waiting area and her sample will be taken to the laboratory for HPV testing using the Xpert HPV Test on the GeneXpert platform (Cepheid, Sunnyvale, CA, USA). This point-of-care test takes approximately one hour to get results. Participants will be asked if they agree with having any remaining sample volume after HPV testing used for future research. If they agree, a future use research informed consent document will be reviewed and signed.

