#### Laboratory procedures at CS da Cidade, CS Urbano, and CS de Chalucuane

Directly following collection of the vaginal self-swab sample, the sample will be placed into a vial with PreserveCyt (ThinPrep System, Hologic Inc, Marlborough, Massachusetts, USA). At a minimum of once per week, samples will be transported to CHC and subsequently tested using the XPert HPV test as described above. Participants will be asked if they agree with having any remaining sample volume after HPV testing used for future research. If they agree, a future use research informed consent document will be reviewed and signed. Results will be picked up the following week when new samples are brought into CHC and distributed to each health facility.

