#### Data collection

Semi-structured interviews will be conducted face-to-face in a quiet and private location and audio recorded. The CFIR framework will be employed to develop an interview guide to generate a robust description of the social, facility culture, personnel factors, and intervention characteristics that influenced successes and/or challenges with implementation. These measures elicit a multi-level emic perspective of the implementation process and suggestions for future improvements. We will assess the degree of implementation uptake (*adoption*) and fidelity (*the degree to which the intervention is delivered as intended*) at each site. Questions designed to elicit data about the intervention’s appropriateness will include provider perceptions of the clinical relevance of the intervention; ease of incorporation into routine workflow; and perception of the value of its continued use.

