#### Analysis plan for qualitative interview

Immediately following each interview, the audio files will be uploaded into a REDCap database. The audio files will be transcribed verbatim and coded by two researchers. Analysts will be blinded to the level of implementation adoption and fidelity to avoid bias. Using NVivo, we will prepopulate all CFIR codes and guidelines to facilitate coder inter-reliability. We will categorize and organize the data as an initial thematic analysis, allowing us to identify recurrent themes and explore interview responses. After each analyst has coded five interviews, they will assess their inter-coder reliability, discussing disagreements in efforts to achieve consensus. If consensus cannot be achieved, PIs [name], [name], and [name] will engage to arbitrate disputes. Our data interpretation objective is to identify constructs that distinguish facilities and/or providers with high and low implementation success, which will provide us information about the constructs that influence implementation and inform future strategy development as we scale up the intervention.

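### The same-day notification component of fidelity is 0% by design at the three peripheral facilities, where the protocol itself plans weekly result reporting

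*Protocol article*

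**What the plan says.** The Statistical analysis plan under Specific objective 2 evaluates fidelity through a Completion Rate, a Test Result Notification Rate and a Treatment Rate. The second is "the proportion of women who were notified of their HPV DNA test result on the same day as sample collection". No exception is made by site, and no weights or rule for combining the three rates are given.

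The planned process differs by site. Table 1 lists it as "HPV result reporting (same-day CHC; weekly in periphery". At CHC the test is run on site: "This point-of-care test takes approximately one hour to get results". For the peripheral facilities the laboratory section says "At a minimum of once per week, samples will be transported to CHC and subsequently tested using the XPert HPV test as described above", and adds that results are collected the week after, when the next batch of samples is delivered.

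Under Specific objective 3, the Data collection section explains fidelity as "the degree to which the intervention is delivered as intended" and assesses it at each site. The analysis plan for the interviews aims to "identify constructs that distinguish facilities and/or providers with high and low implementation success" and blinds the coders to the level of adoption and fidelity.

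**The concern.** Fidelity asks whether a site did what it was meant to do. At the peripheral facilities, what is meant to happen is return of results on a weekly cycle, yet the measure gives credit only for same-day notification. Full adherence and complete failure to notify therefore receive the same score, zero.

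Three things are at stake. The pooled rate has a ceiling below 100% that a reader could take for poor delivery. The rate says nothing about timeliness at the sites where results have to travel and come back. And if the rate is used to describe sites as stronger or weaker implementers in Objective 3, it will set CHC apart from the other three because of laboratory location alone.

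**Working it through.** **Inputs** (Sample size and power calculations, and the text that follows Fig. 4): 280 women per month for 30 months; roughly 6,900 women at CHC; roughly 500 at each of three peripheral facilities.

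**Reproducing the plan's figures.** 280 × 30 = 8,400, and 6,900 + 3 × 500 = 8,400. The total and the site split agree. The protocol states no expected notification rate, so there is none to reproduce.

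**Can a peripheral facility score above zero?** Transport may be more frequent than weekly, and a sample could reach CHC on the day it was taken. Under the written procedure, however, the result is collected only with the following week's delivery, and no other return route is described. The attainable same-day rate is therefore 0 at the periphery and up to 1 at CHC.

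**Pooled ceiling.** Taking women screened as the denominator:

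maximum rate = Σ(site n × attainable rate) / total n = (6,900 × 1 + 1,500 × 0) / 8,400 = 82.1%.

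The women with a structural zero are 1,500/8,400 = 17.9%.

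**Pooled rate for assumed CHC performance** (CHC rate × 6,900/8,400):

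| CHC same-day rate (assumed) | Each peripheral facility | Pooled |
|---|---|---|
| 100% | 0% | 82.1% |
| 95% | 0% | 78.0% |
| 90% | 0% | 73.9% |
| 80% | 0% | 65.7% |
| 70% | 0% | 57.5% |

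**Possible effect on a fidelity summary.** This is an illustration only, because the protocol gives no combination rule. With an equal-weight mean of the three rates, a fully adherent peripheral facility scores (1 + 0 + 1)/3 = 66.7%, against (1 + 1 + 1)/3 = 100% at CHC. With completion and treatment rates equal across sites, the artificial gap is one third of the CHC same-day rate: 0.70/3 = 23 points to 1.00/3 = 33 points for a CHC rate of 70% to 100%.

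**After the change.** If notification is scored against each site's planned turnaround, full adherence gives 100% at all four sites and 100% pooled, and a late result at a peripheral facility lowers the score.

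**The case against.** The strongest reply concerns consequence. The component is one of three, and the Completion Rate and Treatment Rate remain usable everywhere. It does not enter the primary outcome, the power calculation or the interrupted time series. Descriptive statistics are planned by study site, and Table 1 states openly that reporting differs, so a peripheral 0% would probably be read as logistics. About 82% of women are expected at CHC, where same-day notification is the intended process. The framework used in Objective 3 also counts available resources among the factors that may affect fidelity, so laboratory access is a legitimate subject there.

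Most of this stands, and it limits the point. A reader might infer that the protocol marks adherent peripheral facilities as failures, or that Objective 3 ranks sites on this rate. The document does not support either reading. It sets no pass mark, ranks no sites and does not combine the rates, and Objective 3 also draws on adoption, interviews, a survey and contrasts between providers. Nor can it be said that late peripheral results would be invisible to the study as a whole: case report form data are to be documented along the steps of the process, and the form's fields are not shown.

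The reply does not remove the mismatch. Same-day notification could be reported as a timeliness outcome, but the plan labels it fidelity, and the protocol describes fidelity as delivery in line with intention. Site-level tables would make the zero understandable, but they would not make the rate informative at those sites. Nor is this a detail left to a fuller document: the definition is stated, and it conflicts with other stated text.

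**Conclusion.** The point holds as a conflict within the protocol. With perfect delivery, each peripheral facility scores 0% on the notification component (about 1,500 of 8,400 women, 17.9%), and the pooled ceiling is 82.1%. The component cannot distinguish timely from late notification among the peripheral facilities.

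The zero follows from the written return procedure alone. The 82.1% also depends on the approximate site split and on screened women as the denominator; with another split, the ceiling is simply CHC's share of the women. Any effect on Objective 3 is conditional: it arises only to the extent that this component informs the site contrasts, and its size depends on a combination rule that is not stated. The gap of 23 to 33 points is an illustration under equal weights and not a prediction. The primary outcome is unaffected. The definition should be corrected before sites are compared on fidelity.

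**What to change.** Reconcile Table 1, the peripheral laboratory procedures and the Statistical analysis plan:

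- Define the Test Result Notification Rate as the proportion of women notified within their site's planned turnaround: same day at CHC, and the already planned cycle of weekly transport and next-week return at the peripheral facilities.
- Report time from collection to notification by site.
- Keep the same-day rate as a descriptive figure for CHC only.
- Where a notification measure feeds the site contrasts of Objective 3, use the turnaround-based rate.

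This alters measurement only, not sample transport or care. The cost is one changed definition, plus recording the notification date if the case report form does not already capture it.

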Mozambique has one of the highest burdens of cervical cancer in the world, with an age-standardized incidence rate of 50.2 and mortality rate of 38.7 per 100,000 women [12, 13]. Cervical cancer ranks as the most frequent cancer among women in Mozambique, with an estimated 5,300 new cases and 3,800 related deaths reported each year [14]. The prevalence of HIV in women ages 15–49 in Mozambique was estimated at 15.4% in 2021 [15]. Cervical cancer screening was introduced in the country in 2009 using VIA followed by immediate treatment with ablation (cryotherapy or thermal ablation) or referral for LEEP if the cervical lesion(s) did not meet the criteria for ablation [13, 14, 16]. One challenge is that many of the women who screen positive with VIA, are not undergoing treatment with ablation at the same visit. As a result, many women who screen positive are subsequently lost to follow-up and never receive treatment. Most women with cervical cancer in Mozambique therefore present with advanced stage disease and the majority die of their disease.

The current WHO recommendation for cervical cancer screening utilizing primary HPV testing is now being endorsed by the Mozambican Ministry of Health (MOH) [17]. Initial studies showing the feasibility of this approach in the Mozambican context have been encouraging, with women participants reporting a preference for self-sampling approaches [18]. However, these studies to date were conducted amongst eligible women accessing family planning services in higher-resource areas near the nation´s capital of Maputo. Studies designed to evaluate best practices for implementation among a high-risk, lower-resourced population within Mozambique´s already busy HIV care and treatment services are needed to provide the evidence-base required to take this approach to scale.

We summarize below our protocol for a hybrid type III effectiveness-implementation study of HPV self-collection within the HIV care and treatment program in Chókwè District, Mozambique, describing the conceptual frameworks that have guided its development, the different phases that will be employed throughout its implementation, and the measures we propose for evaluating its implementation and effectiveness.

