#### Date collection

Prior to intervention roll-out, baseline data will be retrospectively collected for the prior 12 months at each of the selected study sites, including the number of women accessing care for HIV care and treatment services each month; the number of women screened for cervical cancer through standard of care protocols; the proportion of screen-positive women who then received treatment or referral for treatment, and the length of time between screening positive and receiving treatment, if appropriate. Data will be collected by study team members (physician, nurse, or medical technicians) utilizing a paper-based instrument and then uploaded into a password-protected, tablet-based, online research data capture (REDCap) database. This method allows for the recording of demographic information, medical and medication history, and any pertinent laboratory test results. Data quality control will be conducted by study investigators who will review all completed paper-based study instruments and confirm the accuracy of data entered into REDCap.

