#### Outcome measures

Our primary outcome measure is the number of women screened and the proportion of screen-positive women successfully undergoing treatment. Secondary outcomes measures will include other implementation outcomes (see Specific Objective 3 below), and if successful, will be utilized to inform future research to take this approach to scale across Mozambique.

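### The second interrupted time series models HPV diagnoses, for which no baseline series is listed, while the number of women screened has no before-after analysis

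*Protocol article*

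**What the plan says.** The Outcome measures section defines the primary outcome in two parts: "Our primary outcome measure is the number of women screened and the proportion of screen-positive women successfully undergoing treatment".

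The Statistical analysis plan section gives two interrupted time series. The first uses a logit model to "perform an interrupted time series to assess the impact of the intervention and the proportion of patients who subsequently underwent treatment for cervical cancer", with terms for intervention status, calendar month and their interaction. The second is introduced with "We will again use GLM with a gaussian link to estimate the impact of the intervention on the number of WLWH diagnosed with HPV". It keeps the covariates of the first model (age, CD4 count and viral load are named) and is fitted "following the same steps as above (e.g., another interrupted time series". Ordinal regression is the fallback if normality fails. No model or before-after comparison is named for the number of women screened.

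On the pre-period, the Date collection section says "baseline data will be retrospectively collected for the prior 12 months at each of the selected study sites". One listed item is "the number of women screened for cervical cancer through standard of care protocols". The others are monthly women in HIV care, the share of positive screens that led to treatment or referral, and the delay from a positive screen to treatment. No HPV result or HPV diagnosis count appears. The Background describes existing practice this way: "Cervical cancer screening was introduced in the country in 2009 using VIA followed by immediate treatment with ablation". It presents primary HPV testing as only now gaining ministry endorsement.

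**The concern.** An interrupted time series estimates impact by projecting the pre-intervention trend forward and comparing it with what follows. It needs the same outcome, measured the same way, on both sides of the interruption. HPV DNA testing is itself the intervention, so a count of HPV diagnoses very probably has no pre-intervention counterpart. The number screened does have one, and it is named in the primary outcome, yet no such model is planned for it.

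Two things are at stake. A rise in HPV diagnoses could be reported as an effect against a no-intervention counterfactual when it shows only that a test was introduced. And whether screening volume rose, which the planned baseline data can address, would get no formal answer.

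**Working it through.** **Is there an observed baseline HPV count?** The only pre-intervention figure given for HPV-positive women is the roughly 36% treated under standard of care (Sample size and power calculations). It reproduces as follows:

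- 1,200 visits × 0.52 = 624 women; 624 × 0.75 = 468 aged 25–49; 468 × 0.60 = 280.8, stated as 280.
- 280 × 0.35 = 98 HPV-positive per month.
- 35 ablations per month / 98 = 35.7%, about 36%.

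The denominator of 98 is an assumed count, not an observed one. So this figure does not point to a baseline HPV series either.

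**What the model gives without one.** The terms are intercept, intervention I, month t, and I × t, over 12 pre-months and 30 post-months.

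- *Pre-period absent.* In the 30 post-months I = 1 in every row, so I duplicates the intercept and I × t duplicates t. The design matrix (30 rows, 4 columns) has rank 2. Level and slope change cannot be estimated.
- *Pre-period entered as zero.* The pre-line is fitted at exactly 0 with slope 0, and the projected counterfactual is 0 throughout. The level change is then the fitted number of positives when testing starts, and the slope change is the trend in positives. One simulated series (12 zeros, then 30 Poisson months with mean 98) gave a level change of 100.5 per month (SE 5.3, p < 0.001) and a slope change of −0.07 per month (SE 0.64).

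In the second case the expected level change is women tested × prevalence. At 280 tested per month and the prevalences the article mentions:

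- 25%: 280 × 0.25 = 70
- 35%: 280 × 0.35 = 98
- 40%: 280 × 0.40 = 112

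The apparent effect moves from 70 to 112 per month with no change in the programme's performance.

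**The number screened.** Baseline: 12 months at each site, collected. Post-period: 30 months, planned at about 280 per month overall. With both periods present, all four terms are estimable. The article does not state the current monthly number screened, so the expected change cannot be computed. The nearest planned quantity, the completion rate, is a proportion of enrolled women during implementation and has no baseline.

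**Size of the site-level counts.** The plan also stratifies by facility. About 500 women are expected at each peripheral site over 30 months: 500 / 30 = 16.7 screened per month, of whom 16.7 × 0.35 = 5.8 would be HPV-positive.

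**The case against.** Several stronger readings are tempting, and the documents do not support them.

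- *That half of the primary outcome goes untested.* Table 1 identifies the primary outcome for analysis as the proportion of HPV-positive women treated, and the sample size section powers only that. It has its own time series. The Outcome measures section names one measure with two parts, and the number screened may well be reported descriptively. What stands is that the count has no before-after model, although the article specifies such a model for a different count.
- *That the plan's own figures give 12 months of zeros.* No sentence gives a zero. The baseline list is introduced as non-exhaustive, preliminary HPV prevalence data are cited, and the sites already have GeneXpert expertise. Absence of a baseline series is a strong inference, not a stated fact.
- *That a spurious significant result is certain.* That follows only if zeros are entered. If the series is absent, the model simply cannot be fitted as described.
- *That a Gaussian model is plainly wrong.* At about 98 per month pooled, the normal approximation is reasonable, and a fallback is named. The unit of analysis is not stated, so covariates could enter as monthly summaries. The case for a count model rests mainly on the small site-level series.
- *That only wording needs changing.* Attendance and screening outside the study are not clearly collected after roll-out. The case report form is opened only after consent.

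It can also be said that the number screened after roll-out is partly driven by study enrolment. That is true, but this count has a real baseline, so a change in it can be interpreted.

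**Conclusion.** The concern holds in this form: the second time series is assigned to an outcome that is absent from the listed baseline items and very probably has no pre-intervention series, while the number screened, which has one, is left without a before-after analysis. Depending on how the missing pre-period is handled, the model is either not estimable (rank 2 of 4) or returns a level change equal to the positives found by the new test, about 98 per month at 280 tested and 35% prevalence.

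This rests on VIA having been the screening method at these sites in the 12 months before roll-out and on the listed baseline items being all that bear on HPV. The gap for the number screened does not depend on either assumption. No sample size figure rests on the second series. This is an analysis the article specifies and that would mislead if followed, not detail left to a fuller plan.

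**What to change.** Apply the second interrupted time series to the monthly number of women screened. Use a count model, for example quasi-Poisson or negative binomial with log link, with the log of the monthly number of women in HIV care as offset. That attendance count is already a baseline item; no age band is stated for it, so the same definition must be used in both periods. Leave out patient-level covariates. The count model matters most for the peripheral sites, at about 17 women screened per month.

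Report HPV positivity with a confidence interval, descriptively, in the post-period only. If a baseline HPV series does exist at these sites, add it to the baseline items before modelling the HPV count.

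The cost is small but goes beyond wording. Monthly attendance, and any standard-of-care screening outside the study, must still be extracted from facility records after roll-out. Months in the model participant period, when enrolment is capped at 1–2 per day, should be flagged or excluded.
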